##### Type of analyses

All variables will be described globally and by group (donors included during the “before” versus “after” period). The description will include the numbers and percentages of the modalities for the qualitative variables and the minimum, maximum, mean, standard deviation and median for the quantitative variables.

The one-year overall mortality rate will be estimated for the two periods (before and after intervention). This will be modeled by a mixed-effects logistic regression allowing for the cluster (hospital) level as a random effect and the recipient as a fixed effect. The same type of analysis will be used for binary variables.

Quantitative variables will be modeled by mixed linear models.

The total duration of the decision-making process and the duration between the first proposal and the transplantation will be analyzed by a proportional-risk Cox model with random effects.

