#### Inclusion criteria

Organs from a brain-dead donor among: kidney, liver, heart and lung.Donor age over 18Deceased in France

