#### Statistical analyses

##### Sample size

In 2015, there were a total of 5746 transplants from deceased donors (heart: *n* = 471; lung: *n* = 345; liver: *n* = 1355; kidney: *n* = 2939). 335 (15.4%) vital organs (heart, lung, liver) proposed to transplant teams were finally not transplanted. 297 (10.1%) kidneys were collected but not transplanted.

Our hypothesis is that image transfer will reduce lost organs by 82 (11.6%) for vital organs (heart = 20, lung = 17, liver = 45) and about 100 (6%) for kidney.

With a probability of Type I Error of 0.05 and a Power a 90%, the sample size required is 1797 vital organs transplantations and 924 kidney transplantations, which is inferior to our estimated cohort size of deceased donors.

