## Discussion

This study was initially planned to start very early after the end of the technical implementation of “Cristal Images”. But technical implementation does not correlate well with professional adoption [13, 14], for reasons such as behavioral barriers, change management, resistance to change, social acceptability of teleimaging or organizational barriers, which emphasizes the necessity for teleimaging services to nicely fit into existing organizational structures.

The impact of telemedicine should be evaluated when it is routinely used by professionals [15]. However, there is no proper definition of the routine use. That means that we may need to modify the beginning of the period after intervention regarding the data that we will get about the “Cristal Images” uptake. However, as this study is funded by the French Ministry of Health, results are expected within 5 years, implying constraints on the time for the ‘after’ period.

Another potential issue for the evaluation is that we considered the transplantation process as a single process, regardless of the organ and the team. The procurement process differs between vital organs (heart, liver, lung) and kidney in the transplantation process: kidneys can be extracted by the local team and exported by courier service to the transplant team. Vital organs are ordinarily extracted by the transplant team. Moreover, depending on the organs, the teams do not require the same types of imaging, and there may be heterogeneity about availability of imaging (e.g. the full-body CT-scan, required by lung transplant teams, is often available, and cardiac ultrasound or coronary angiography are less available, because of technical issues or non-realization of the imaging). Therefore the utility of real-time visualization may vary with respect to organs and across transplant teams. This may have an impact on several endpoints and will be accounted for accordingly. This study will be a unique occasion to show such variations in the uptake and uses of the technology.

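### The binary-outcome model names only a hospital random effect, so where organs from one donor are analysed together the before/after standard error ignores within-donor correlation

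*Protocol article*

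**What the plan says.** Under Type of analyses, the protocol gives the model for one-year mortality: "This will be modeled by a mixed-effects logistic regression allowing for the cluster (hospital) level as a random effect". The same sentence enters the recipient as a fixed effect, and the next sentence extends this type of analysis to binary variables generally. No donor effect, hospital-by-period effect or robust variance is named. Quantitative outcomes get mixed linear models and durations get a Cox model with random effects, in both cases without stating the levels.

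The Inclusion criteria make the organ the unit: "Organs from a brain-dead donor among: kidney, liver, heart and lung". The Design section describes an uncontrolled comparison of 2015–2016 with 2018–2019, and Type of analyses defines the two groups by the period in which the donor was included. The Discussion expects differences between teams: "Therefore the utility of real-time visualization may vary with respect to organs and across transplant teams". It then undertakes to allow for this variation, without saying how.

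**The concern.** Organs from one donor share that donor's age, co-morbidity and cause of death, so non-collection, discard and graft outcome may be correlated within donor. Because no donor contributes to both periods, this correlation does not cancel in the before/after difference and adds to its variance.

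A hospital intercept does not absorb it on either reading of hospital. If the transplant hospital is meant, one donor's organs can go to different hospitals. If the procurement hospital is meant, donors are nested below it and keep their own residual correlation. Recipient terms do not help, since organs from one donor go to different recipients.

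A hospital intercept also removes only the stable level of each hospital, not a change specific to that hospital between periods. At stake are the width of the intervals and the real type I error of the period effect, which carries the whole inference in an uncontrolled design.

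**Working it through.** **1. The plan's own figures.** The Sample size section sets "With a probability of Type I Error of 0.05 and a Power a 90" per cent and concludes that "the sample size required is 1797 vital organs transplantations and 924 kidney transplantations". Its inputs are "335 (15.4%) vital organs (heart, lung, liver) proposed to transplant teams were finally not transplanted", "297 (10.1%) kidneys were collected but not transplanted" and the hypothesis that "image transfer will reduce lost organs by 82 (11.6%) for vital organs", with 6% for kidney.
- Vital organs in 2015: 471 + 345 + 1355 = 2171. Before: 335/2171 = 15.4%. After: (335 − 82)/2171 = 253/2171 = 11.65%, so the 11.6% reads as the after-period loss rate.
- Kidney, 10.1% against 6%, two-sided 0.05, power 90%, pooled two-proportion formula for independent observations: 924 per period, an exact match.
- Vital organs, same formula with continuity correction: 1750 from the rounded percentages and 1776 from the counts, against 1797 stated (2.6% and 1.2% off). Without the correction: 1698 and 1723.

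So the kidney figure is an independence calculation, the vital-organ figure is close to one, and no clustering allowance is stated for either.

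**2. Donor clustering.** With m organs per donor and within-donor correlation ICC, the variance of each period's proportion is multiplied by DEFF = 1 + (m − 1) × ICC. Both periods carry this factor and share no donors, so the contrast carries it too. If the model omits it, the true standard error is √DEFF times the reported one, and the real two-sided error is 2 × [1 − Φ(1.96/√DEFF)]. The values of m and ICC are assumptions.

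| m | ICC | DEFF | √DEFF | Real type I error |
|---|---|---|---|---|
| 2 | 0.05 | 1.05 | 1.025 | 5.6% |
| 2 | 0.10 | 1.10 | 1.049 | 6.2% |
| 2 | 0.20 | 1.20 | 1.095 | 7.4% |
| 2 | 0.30 | 1.30 | 1.140 | 8.6% |
| 2 | 0.50 | 1.50 | 1.225 | 11% |
| 3 | 0.05 | 1.10 | 1.049 | 6.2% |
| 3 | 0.30 | 1.60 | 1.265 | 12.1% |

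With 1.5 organs per donor on average and ICC 0.30, DEFF is 1.15 and the error 6.8%. With one organ per donor, or ICC 0, it is 5%.

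Simulation under no period effect agrees. With a donor standard deviation of 1 on the logit scale and two organs per donor, a hospital-adjusted linear model (a stand-in for the logistic one) rejected in 7.1% of 1,500 runs, against 5.6% with no donor effect. A second simulation (4,000 runs, 40 hospitals, 146 kidneys per hospital and period, loss 10%, donor ICC 0.5) gave 11.1%, against 4.4% with none.

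**3. Hospital-by-period drift.** The protocol gives no number of hospitals, hospital ICC (ρ) or between-period correlation (CAC). Assume 45 hospitals and 2 × 2171 = 4342 vital organs per period, so m = 4342/45 ≈ 96.5. The ratio of true to intercept-only variance is [1 + (m − 1)ρ − mρ × CAC]/(1 − ρ).
- CAC 1: ratio 1, error 5%.
- CAC 0.9, ρ 0.01 to 0.05: standard-error ratio 1.05 to 1.23, error 6.1% to 11.0%.
- CAC 0.8, same ρ: ratio 1.09 to 1.42, error 7.3% to 16.7%.

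These values only illustrate how strongly the result depends on what is assumed.

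**4. Power for organ loss.** At the 2015 rates there are 2 × 2939 = 5878 kidneys per period; at DEFF 1.5 the effective number is 5878/1.5 ≈ 3919, against 924. For vital organs at DEFF 1.6 it is 4342/1.6 ≈ 2714, against 1797. These are all transplants from deceased donors, so the eligible cohort may be smaller. For organ loss, error rate and interval width are the issue, not power.

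**The case against.** The strongest reply is that a journal article compresses the analysis plan. The text commits to handling clustering, naming hospital does not exclude further terms, and the Discussion undertakes to allow for variation between organs and teams. That carries weight for the linear and Cox models. A reader might infer that every model has a hospital effect alone, but the text does not say so; their levels are simply open. It carries less weight for binary outcomes, where a level was chosen and named and the donor was not. The Discussion's undertaking concerns organs and teams, not shared donors, and names no method.

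Second, donor clustering arises only when organs sharing a donor enter the same model. The sample size separates kidneys from vital organs, and a model for hearts or livers alone would have little of it. This stands and limits the point.

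Third, the ICCs are assumed. An ICC of 0.5 may be conceivable for discard of paired kidneys, but nothing supports it for graft survival, the primary endpoint. This stands: the inflation is conditional and may be slight.

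Fourth, a reader might take the expected differences between teams as proof that type I error is inflated. They are not. Differing uptake and benefit are heterogeneity of the intervention's effect, which vanishes if there is no effect anywhere. Only hospital-specific drift unrelated to the platform would inflate the error by this route, and the protocol gives no evidence of its size. The registry is also exhaustive: if the target is the average change in these particular hospitals, a random period effect by hospital is not automatically needed.

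**Conclusion.** The point holds for binary-outcome models that combine organs from one donor. There the stated structure omits a correlation that adds directly to the variance of the period effect. Assuming two organs per donor and ICC 0.05 to 0.5, the real type I error is about 5.6% to 11%, and a nominal 95% interval covers about 94% down to 89%. The primary endpoint is affected only if it is analysed as a binary variable with such organs together, and then in proportion to an ICC that is not known.

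The hospital-by-period part is weaker. It matters if hospitals drift differently for reasons unrelated to the intervention and the result is meant to generalise beyond them. The size is unknown, so it justifies a sensitivity analysis rather than a change to the main model. The documents do not support a claim that all standard errors are too small, or that every binary endpoint is tested at several times the nominal level.

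**What to change.** - In binary-outcome models that combine organs from one donor, add a donor random effect or use donor-clustered robust variance. State whether hospital means the procurement or the transplant hospital: in the latter case donors and hospitals are crossed, and the method must allow for that.
- Prespecify a sensitivity analysis with a hospital-by-period random effect, and say whether the target is the change in these hospitals or in a wider population.
- State the random-effect levels for the linear and Cox models, including donor where organs sharing a donor are combined.

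The cost is some wording, slightly heavier fitting and somewhat wider intervals (1.02 to 1.22 times under the assumptions above). A donor random effect may be hard to estimate with only one or two organs per donor, and how well it fits here has not been tested; robust variance is then the simpler choice. No additional data collection should be needed if the extraction identifies which organs share a donor.

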### Preference elicitation study

#### Participants and data source

Our data will be collected using questionnaires addressed to transplant teams. All the transplant teams working in hospitals authorized by the Regional Health Agencies (“ARS”) on the advice of the French Agency of Biomedicine (ABM) to perform kidney, liver, heart or lung transplant will be contacted for inclusion in the study, excepted the transplant teams working in pediatric hospitals or in hospitals located in French overseas departments, who will be excluded of the study to align with the main evaluation protocol. The questionnaires will include items about the preferences of the professionals regarding “Cristal Images” (utilization, components, evolutions) as well as questions to gather information on the activity of the respondents, such as their clinical specialty, the size of their hospital and team, the number of transplantations operated per year, their practice with “Cristal Images” etc.

#### Method

An extensive review of the literature about preference elicitation methods was conducted beforehand, that allowed us to classify methods and to choose the Best Worst Scaling (BWS) methods, introduced by Finn and Louviere [8] and designed by Marley and Louviere [9], as the most relevant ones for our study (Fig. 1).

**Fig. 1 Fig1:**
[figure not shown]
Classification of preference elicitation methods

Revealed preference methods are based on the observation of actual utilization patterns; these methods are not applicable here, especially because our objective is to study how actual preferences relate to advisable evolutions of “Cristal Images”. Stated preference methods consist in asking respondents to choose between hypothetical situations in order to elicit their preferences. Among the different stated preference methods, we privileged quantitative methods because we can measure the relative strength of the different preferences and their relationships. Among them, the choice-based techniques are the closest to the decision-making process of professionals in their daily practices. From a research perspective, these methods imply a lower cognitive burden and a greater wealth of information. Methods based on the random utility theory have a strong theoretical basis, namely that an individual’s utility includes a systematic observable component and a random unobservable component [10]. Finally, among the random utility theory, Discrete Choice Experiment (DCE) and Best-Worst Scaling (BWS) have received extensive application in health in the 2000s–2010s, compared to the trio-wise method that is currently more cutting-edge. BWS optimizes the cognitive burden for respondents and the wealth of information; it also allows to directly compare attributes and finally, for Best-Worst DCE, to get a maximal amount of data for a given number of respondents. In sum, we pre-selected two BWS designs: Best-Worst Attribute Scaling and Best-Worst DCE.

#### Design

In a BWS design, the variable of interest is decomposed into attributes, each with different levels, and respondents are asked to identify their extreme preferences (best and worst items), among attribute levels within a single profile (Best-Worst Attribute Scaling) or among different profiles described by a number of attributes fixed at specific levels (Best-Worst DCE) [11, 12]. This enables comparison between the relative preferences for attributes and levels of a given object, namely the teletransmission of imaging in the transplantation process (“Cristal Images”) in this study.

Therefore, to design a study of preference elicitation based on the Best-Worst Attribute Scaling or the Best-Worst DCE methods, we need to determine the attributes and their levels corresponding to actual or potential characteristics of the intervention that transplant teams may value. To identify them, a qualitative study has been carried out from July 2018 to March 2019. Semi-directed phone interviews were conducted with professionals working in transplant teams included in the study. The sampling of this qualitative phase privileges diversity over representativity. Three to five interviews have been made per organ as well as per region (4 regions following the classification by the Regulation and Support Service (“SRA”) of the ABM), for a total of 16 interviews. The sampling also takes into account the number of transplantations performed per year by transplant teams as well as the role and the hierarchical position of interviewees. Interviews are transcribed for the purposes of the qualitative analysis to determine attributes and levels for the BWS design. The qualitative analysis will also guide the selection of the most appropriate design between Best-Worst Attribute Scaling and Best-Worst DCE.

## Discussion

This study was initially planned to start very early after the end of the technical implementation of “Cristal Images”. But technical implementation does not correlate well with professional adoption [13, 14], for reasons such as behavioral barriers, change management, resistance to change, social acceptability of teleimaging or organizational barriers, which emphasizes the necessity for teleimaging services to nicely fit into existing organizational structures.

The impact of telemedicine should be evaluated when it is routinely used by professionals [15]. However, there is no proper definition of the routine use. That means that we may need to modify the beginning of the period after intervention regarding the data that we will get about the “Cristal Images” uptake. However, as this study is funded by the French Ministry of Health, results are expected within 5 years, implying constraints on the time for the ‘after’ period.

Another potential issue for the evaluation is that we considered the transplantation process as a single process, regardless of the organ and the team. The procurement process differs between vital organs (heart, liver, lung) and kidney in the transplantation process: kidneys can be extracted by the local team and exported by courier service to the transplant team. Vital organs are ordinarily extracted by the transplant team. Moreover, depending on the organs, the teams do not require the same types of imaging, and there may be heterogeneity about availability of imaging (e.g. the full-body CT-scan, required by lung transplant teams, is often available, and cardiac ultrasound or coronary angiography are less available, because of technical issues or non-realization of the imaging). Therefore the utility of real-time visualization may vary with respect to organs and across transplant teams. This may have an impact on several endpoints and will be accounted for accordingly. This study will be a unique occasion to show such variations in the uptake and uses of the technology.

The preference elicitation study will generate evidence on the drivers and hurdles to an appropriate integration of the technology by transplant teams. It will also bring out the needs of these teams, current limitations of the teleimaging tool and prospects for further developments. Ultimately, we hope that professionals’ involvement in the preparatory phase will be instrumental to improve the uptake of transplant teams in the preference elicitation study.

Finally, the research, based on the mixed methods study, will provide stakeholders with data on efficiency of real-time visualization for transplant teams and identify the levers likely to influence the technology use among these teams.

## Data Availability

The datasets which will be analyzed during the current study will not be publicly available, as the French data protection law (Loi “Informatique et Libertés”) forbids to share data or to make it publicly available, even if they have been unidentified previously. Furthermore, the transfer of the data outside EU is not possible without getting a new specific authorization of the authority in charge of the enforcement of the “Informatique et Liberté” Law (named CNIL: https://www.cnil.fr/en/home). Therefore, an authorization must be granted by the CNIL before data can be made available; once this authorization obtained, data will be available upon request to DRCI-URC Eco (www.urc-eco.fr, [contact]).

## Abbreviations

ABM: Agency of Biomedicine
ARS: Regional Health Agency
BWS: Best-Worst Scaling
DCE: Discrete Choice Experiment
SRA: Regulation and Support Service
